### Rationale for primary endpoint

Extubation failure is a clinically relevant short-term outcome consistent with VILI’s etiological role in BPD. However, there are no universally accepted criteria for intubation in this population. We therefore define the primary outcome as extubation failure using objective clinical physiological criteria rather than a practice-based outcome such as re-intubation, which could be susceptible to performance bias in this unblinded trial. This is consistent with other high-quality trials of respiratory management in the neonatal literature [26–28].

### Secondary study endpoints

The DIVA trial is not powered to identify the impact of NIV-NAVA on all later respiratory outcomes. However, exploratory analyses of the impact of NIV-NAVA on respiratory outcomes and the association between timing and occurrence of extubation failure on longer-term respiratory morbidity among extremely preterm infants will be conducted. Enrolled infants will be followed until 36 weeks PMA for the following secondary outcomes:Bronchopulmonary dysplasia at 36 weeks PMA, as defined by Jensen et al. [29]Composite of death/BPDEndotracheal intubation, including time and reason for intubationPMA at last mechanical ventilation, last positive pressure, and last supplemental oxygenPost-randomization postnatal steroidsBrain injury (intraventricular hemorrhage and periventricular leukomalacia)Patent ductus arteriosus requiring therapyPulmonary hemorrhageCulture proven sepsisNecrotizing enterocolitisRetinopathy of prematurityTime to deathAir leaksGastrointestinal perforation or bleeding

## Participant timeline {13}

### Duration of study participation

Figures 1 and 2 outline the timing of enrollment, trial interventions, and data collection. Subject participation will commence upon enrollment following informed consent in the trial, as early as 24 weeks PMA, and will continue until all secondary outcomes are ascertained by 36^6/7^ weeks PMA. Thus, the total duration of study participation will be up to 13 weeks for each study subject.

**Fig. 2 Fig2:**
[figure not shown]
Schedule of enrollment, interventions, and assessments (SPIRIT figure). Abbreviations: FiO_2_, fraction of inspired oxygen; H, hours; PMA, post-menstrual age; wks, weeks. Asterisk symbol (*) indicates the following: for run-in phase, all enrolled infants are allocated to NIV-NAVA at randomization and data collection ends after 5 days of extubation

### Sample size {14}

The calculated study sample size accounts for 478 infants in the randomization phase. Very little published data exists for reintubation rates using NIV-NAVA or NS-NIPPV in our study population. In a recent pilot RCT of more mature preterm infants (median 27 weeks’ gestation), 9% of infants managed with NIV-NAVA were reintubated within 5 days [30]. Our preliminary data indicates a higher failure rate in our more immature study population (Table 1). Sample size estimates were based on having 90% power to detect a 15% absolute risk reduction in extubation failure among infants treated with NIV-NAVA, compared with non-synchronized NIPPV, assuming a two-sided test, family-wise error rate of 0.05 and a group sequential design with 2 interim analyses. The interim analyses were set after 50% and 75% of the infants have completed the primary outcome and used Len-DeMets spending functions of the O’Brien-Fleming type. Simulation studies were used to determine that interim analyses prior to 50% completion of the primary outcome were highly unlikely to result in any clinically meaningful differences in the primary efficacy and safety outcomes while reducing power for the final analysis.

Preliminary data from the DIVA trial sites informed sample size calculations: following extubation, 40% of infants treated with NS-NIPPV were reintubated within 5 days, and 19% of infants treated with NIV-NAVA were reintubated within 5 days (Table 1). This reintubation rate for NS-NIPPV is consistent with the reintubation rate of 37% among infants treated with NIPPV in the largest trial of NIPPV vs. CPAP (*n* = 1009) [19].

Thus, we conservatively anticipate a 5-day extubation failure rate of 35% in the NS-NIPPV group. We assume *90% power* and a two-sided proportions test. To detect a 15% absolute reduction in the rate of extubation failure rate in the NIV-NAVA group would require 406 infants. We expect 25% of enrolled infants to be from a multiple birth (based on the PIs’ previous trials and published papers). The multiple birth design effect is 1.15, assuming an intraclass correlation coefficient of 0.6. Inflating the required sample size for the design effect and conservatively allowing for 2% drop-out prior to the primary outcome results in 478 randomized infants (Table 4).

**Table 4 Tab4:** Sample size requirements for the primary outcome

Power	Failure rate in non-synchronized NIPPV arm	Failure rate in NIV-NAVA arm	GSD sample size	ICC	Design effect	Sample size (total infants randomized)
90%	30%	15%	358	0.4	1.10	402
				0.6	1.15	422
		20%	844	0.4	1.10	948
				0.6	1.15	992
	35%	15%	222	0.4	1.10	250
				0.6	1.15	262
		20%	406	0.4	1.10	456
				0.6	1.15	478
	40%	15%	154	0.4	1.10	174
				0.6	1.15	182
		20%	246	0.4	1.10	278
				0.6	1.15	290

Only infants in the randomization phase will be included in the analysis of NIV-NAVA vs. NS-NIPPV for specified outcomes; infants from the run-in phase do not contribute to the analysis. We anticipate enrolling (consenting) up to two infants for every infant who meets all eligibility criteria and is allocated to treatment, as not all consented subjects will be eligible for the trial at the time of extubation. Thus, we expect to enroll (consent) up to 1080 infants to obtain 540 eligible subjects allocated to study treatment across both phases.

### Recruitment {15}

All study participants will be inpatients in the neonatal intensive care unit (NICU) at sites experienced in clinical trials. These sites have existing screening and consent procedures for neonatal trials, which include daily queries of new NICU admissions to identify and follow potentially eligible subjects. Parents of potentially eligible infants will be approached by a member of the clinical study team as soon as possible after birth to offer study participation, allowing for treatment allocation at the time of later clinical extubation if within the first 28 days of life.

## Assignment of interventions: allocation

### Sequence generation {16a}

An online, electronic data management system (DMS) randomization module, including a randomization form, will generate the sequence for randomization, maintaining a balance between treatment arms using randomly permutated blocks. Randomization is stratified by site, gestational age group (24–25^6/7^, 26–27^6/7^ weeks), and time on mechanical ventilation prior to extubation (≤ 7 days, > 7 days), in a 1:1 allocation. Twins and multiples will be randomized individually. Each participant will only be randomized once.

### Concealment mechanism {16b}

In order to protect allocation concealment, randomization occurs as close as possible to the clinical decision to extubate an eligible infant (or to provide a trial of non-invasive support after unplanned extubation). Allocation is blinded prior to randomization.

### Implementation {16c}

The DMS randomization module requires site staff to enter eligibility confirmation data to verify the appropriateness of randomization. In particular, the availability of a ventilator capable of providing either support mode will be confirmed before randomization occurs. Once infant eligibility and equipment availability are confirmed, the module will perform the randomization, record the assignment to the subject, and display the treatment arm on the screen for the site staff.

## Assignment of interventions: blinding

### Who will be blinded {17a}

The study will be blinded in treatment allocation; patients, parents, and clinicians will be unblinded once treatment is assigned, and then, they are blinded to the analyses. Since this technology is visible, this trial is unblinded to the infant’s clinical team.

### Procedure for unblinding if needed {17b}

This trial is unblinded. Analyses will be unblinded once all outcome comparisons are completed.

## Data collection and management

### Plans for assessment and collection of outcomes {18a}

#### Study measures

Study measures will be ascertained from the maternal and infant medical records or collected from ventilator logs. Key data to be collected for all subjects allocated to treatment are listed in Table 5.

**Table 5 Tab5:** Key data to be collected for enrolled subjects

Topic and timing	Specific data elements
Pre-randomization characteristics	*Demographics*: birth weight, gestational age at birth, sex, race, ethnicity, multiple gestations, small for gestational age at birth, postnatal age at randomization *Maternal characteristics*: antenatal steroids, clinical diagnosis of chorioamnionitis, diagnosis of PPROM, mode of delivery *Postnatal interventions*: surfactant (number, timing, and method of administration), postnatal steroids *Respiratory interventions*: duration of mechanical ventilation, mode of ventilation and highest settings, ventilator settings at the time of extubation, postnatal age (days) at extubation, interval (hours) between extubation and initiation of allocated ventilator mode
Daily respiratory status, obtained daily for the first 5 days after treatment allocation	*Extubation failure criteria*: blood gas values, highest FiO_2_, number of apnea/bradycardia events over the previous 24 h Intubation, including timing and indication All respiratory settings and FiO_2_ values
Respiratory Status obtained weekly from treatment allocation until 36 weeks PMA	Timing and indication for all intubations Timing of extubation Start/stop dates of modes of support (i.e., invasive ventilation, non-invasive ventilation, CPAP, cannula, room air) Respiratory medications, including diuretics and postnatal steroids PMA at last invasive ventilation, positive pressure, and supplemental oxygen
Respiratory status at 36 weeks PMA	Respiratory support mode and settings at 36 weeks PMA Supplemental oxygen at 36 weeks PMA
Safety outcomes by 36 weeks PMA	Air leaks, GI perforation and bleeding, and death (date and primary cause of death; narrative autopsy results if performed)
Secondary clinical outcomes by 36 weeks PMA	Brain injury, retinopathy of prematurity, sepsis, patent ductus arteriosus, pulmonary hemorrhage, necrotizing enterocolitis Any surgical procedures

### Plans to promote participant retention and complete follow-up {18b}

The study follow-up phase will commence after primary outcome ascertainment and continue until 36 weeks PMA, death, or hospital discharge/transfer (whichever is first). Only randomized patients will be followed (there will be no follow-up for patients in the run-in phase).

For subjects whose parents withdraw consent to participate in the study, the study team will request permission for ongoing collection and use of study-related measures and endpoints from the medical record*.*

### Data management {19}

Project and data management support will be provided by the research team at the University of Pennsylvania Clinical Research Computing Unit and biostatisticians at the University of Virginia (UVA). Initial stages of data management will be done by experienced clinical data managers and database developers, supported by computer system analysts, programmers, and information technology specialists. These personnel will be responsible for data quality and timeliness, documentation of processes and procedures, and training of data management staff.

### Data security

Each site will maintain its screening logs with identifiable information. Only dates (from protected health information) will be shared with the data coordinating center (DCC). Each site will directly enter all data into the securely maintained DCC REDCap DMS.

### Confidentiality {27}

The DIVA study confidentiality procedures are designed to protect potential participants and ensure the confidentiality, security, and integrity of all data collected for this trial.

### Plans for collection, laboratory evaluation, and storage of biological specimens for genetic or molecular analysis in this trial/future use {33}

The trial involves no plans for collection, laboratory evaluation, and storage of biological specimens for genetic or molecular analysis.

## Statistical methods

### Statistical methods for primary and secondary outcomes {20a}

The proposed study is a two-arm parallel design of two alternative courses of treatment. A modified “as-randomized” analysis (or “intention-to-treat” analysis) (mITT) will estimate whether NIV-NAVA is superior to NS-NIPPV in avoiding treatment failure and is at least as good as NS-NIPPV in avoiding adverse events.

Among infants randomized before extubation, there is a risk that infants will become ineligible for extubation (and from the trial) after randomization due to changes in clinical status. Therefore, a mITT analysis has been planned. Only infants whose eligibility changes due to new/emergent conditions not known at the time of randomization will be excluded from the primary outcome analysis set in the mITT analysis. This number is expected to be minimal and will be closely monitored. A sensitivity analysis using a conventional ITT analysis will also be conducted.

The primary outcome will compare rates of extubation failure between the treatments using logistic regression. The regression model will be fitted using robust clustered standard errors under the generalized estimating equation (GEE) framework, with an exchangeable correlation structure for clusters based on infant mother, i.e., adjusting for the inherent correlation between infants that are multiples. The primary analysis will include clinical site, gestational age, biological sex, and days of invasive ventilation prior to extubation as fixed effects, to control for any residual confounding and site-level treatment imbalance from the stratification factors. Standard regression diagnostics will be used to assess model adequacy and to examine for potential outlying or influential data points.

Secondary efficacy and safety outcomes will be analyzed using similar procedures to the primary outcome. Comparisons between treatment arms will use GEE based logistic regression (dichotomous outcomes), linear regression (continuous outcomes), Poisson regression (count outcomes), or survival analysis (time based outcomes), as appropriate.

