### Objectives {7}

The primary objective is to compare rates of extubation failure within 5 days of extubation between extremely preterm infants treated with NIV-NAVA to those treated with NS-NIPPV.

The secondary objective is to compare respiratory and safety outcomes through 36 weeks postmenstrual age (PMA) among infants treated with NIV-NAVA vs. NS-NIPPV.

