### Adverse event reporting and harms {22}

Adverse events will be monitored during the study intervention and follow-up phases to ensure timely detection of events that may affect safety or continued participation. Reportable events will be reported to the DCC, who will then ensure all events are reported to the IRB and DSMB.

Pre-specified reportable trial SAEs include:New air leaks (pneumothorax or pulmonary interstitial emphysema)New gastrointestinal perforation or bleeding (theoretical concern from Edi catheter)Death

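### The safety aim is worded as non-inferiority, but the analysis assigned to it is an ordinary between-arm comparison with no stated criterion

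*Protocol article*

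**What the plan says.** The protocol article, under Statistical methods for primary and secondary outcomes {20a}, gives the modified intention-to-treat analysis two aims in one sentence. It "will estimate whether NIV-NAVA is superior to NS-NIPPV in avoiding treatment failure", and whether it "is at least as good as NS-NIPPV in avoiding adverse events".

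Two paragraphs later the same section gives the method: "Secondary efficacy and safety outcomes will be analyzed using similar procedures to the primary outcome". For binary events this means a GEE logistic model comparing the arms.

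Three other places bear on the aim:

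- Objectives {7} uses plainer terms: "The secondary objective is to compare respiratory and safety outcomes through 36 weeks postmenstrual age (PMA". It has no wording about being no worse.
- Adverse event reporting and harms {22} names three pre-specified serious events: air leaks, gastrointestinal perforation or bleeding, and death. The second is flagged there as a theoretical concern from the Edi catheter.
- Secondary study endpoints carries a caveat on power: "The DIVA trial is not powered to identify the impact of NIV-NAVA on all later respiratory outcomes". It speaks of later respiratory outcomes and does not clearly reach the serious events.

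The article gives no expected rate for any of these events, no tolerated excess risk and no rule on a confidence bound.

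**The concern.** Being no worse than a comparator is a non-inferiority proposition. Supporting it takes a largest acceptable excess and an interval that excludes anything larger. A comparison built to detect a difference answers another question: when it is not significant, the data may still be compatible with substantial harm. The section therefore states one question and assigns a method that answers another, and the objective in {7} matches the method, not the aim.

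This matters because at least one named event is a suspected harm of the experimental device. An over-reassuring reading would favour the experimental arm, and the wording of {20a} leaves that reading open to anyone reporting or citing the trial.

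**Working it through.** **1. What the sample size was built for.** Inputs from Sample size {14}: failure 35% against 20%, two-sided 0.05, 90% power, looks at 50% and 75% with O'Brien-Fleming-type spending, design effect 1.15, drop-out 2%.

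- The fixed-sample two-proportion formula without continuity correction gives 370 in total; with continuity correction it gives 396.
- The spending bounds are about 2.963, 2.359 and 2.014, and the sample size inflation is 1.0183. So 396 × 1.0183 = 403, close to the stated 406.
- 406 × 1.15 = 466.9, rounded up to 468; 468 / 0.98 = 477.6, giving the stated 478.

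The plan's figure reproduces. Every input concerns extubation failure; none concerns an adverse event.

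**2. Infants available for a safety comparison.** With 1:1 allocation, 478 / 2 = 239 per arm. If the plan's drop-out and design effect also applied to safety outcomes, 239 × 0.98 / 1.15 = 203.7, taken as 203. Applying them is an assumption, so both ends are shown.

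**3. How often a difference test misses a true doubling.** Base rates p are assumed. The test is an unadjusted two-sided 5% test with n per arm, p₁ = p, p₂ = 2p and p̄ = 1.5p:

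power = Φ{ [p − 1.96 √(2p̄(1−p̄)/n)] / √([p₁(1−p₁)+p₂(1−p₂)]/n) }

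Example at 5% against 10% with n = 239: the standard error is √(2 × 0.075 × 0.925 / 239) = 0.0241 under no difference and √((0.0475 + 0.09) / 239) = 0.0240 under the doubling. So z = (0.05 − 1.96 × 0.0241) / 0.0240 ≈ 0.12, power is about 0.55, and the test misses about 45% of the time.

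**4. What the interval would look like if the true rates were equal.** Half-width = 1.96 √(2p(1−p)/n). At 5% and 239 per arm: 1.96 × √(2 × 0.05 × 0.95 / 239) = 3.9 points. Upper limit of the risk ratio ≈ exp{1.96 √(2(1−p)/(np))}.

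| Assumed base rate | Misses a true doubling | 95% half-width, equal rates | Upper risk-ratio limit, equal rates |
|---|---|---|---|
| 2% | 75–78% | 2.5–2.7 points | 3.5–3.9 |
| 5% | 45–52% | 3.9–4.2 points | 2.2–2.3 |
| 10% | 13–19% | 5.4–5.8 points | 1.7–1.8 |
| 20% | under 1% | 7.2–7.8 points | 1.4–1.5 |

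In each range the smaller figure is for 239 per arm and the larger for 203.

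**5. What keeping the claim would require.** With a 5-point margin, used only for illustration, the chance of showing non-inferiority when true rates are equal is Φ(0.05/SE − 1.96), where SE = √(2p(1−p)/n). This is 95–97% at a 2% rate, 64–71% at 5%, 39–45% at 10% and 24–28% at 20%. At a 2% base rate that margin would tolerate 7%, or 3.5 times the base rate. One margin would therefore not suit every event.

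**The case against.** A reader might infer that the plan will declare NIV-NAVA safe whenever the safety comparison is not significant, so that about 45% of trials with a true doubling from 5% would report it as no worse. The document does not support this. Its verb is to estimate whether, which poses a question and sets no decision rule. The regression models yield effect estimates and intervals as well as p-values, so a null test is not the only basis on which the question could be judged. No passage says that a null result will be taken as evidence of safety. The 45% is the chance of no significant difference, not of a declaration of safety.

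A reader might also infer that the trial is underpowered for safety in general. That depends on rates that the article does not give. From a 10% base rate a doubling is detected with about 81–87% power.

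A margin or criterion may also stand in the full protocol or SAP, which are not shown, so its absence from the article is not by itself an error. Safety is overseen by an independent monitoring board too, and does not rest on one final test.

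All of this stands, and it limits the point without removing it. The article itself states a non-inferiority-type aim, assigns it a superiority-type comparison, and words its formal objective differently. That mismatch is in the published text whatever the SAP contains.

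**Conclusion.** The point holds as a mismatch between aim, analysis and objective. The safety aim in {20a} asks for more than the assigned comparison or the sample size was designed to deliver, and more than {7} sets out to do. The wording permits a null result to be read as safety, though it does not prescribe that reading.

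The size depends on assumed event rates, an unadjusted test of two proportions, and 203 to 239 infants per arm. For events at about 5% or below, a null result would be weak evidence: a true doubling is missed roughly half to three-quarters of the time, and with equal 5% rates the interval would still reach a risk ratio above 2. At 10% and above, concern about missing a doubling fades, but the mismatch in wording remains.

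**What to change.** Reword the safety aim in {20a} so that it agrees with {7}. For example:

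> Adverse event rates will be compared between arms with effect estimates (including the risk difference) and two-sided 95% confidence intervals. Absence of a significant difference will not be interpreted as equivalence or non-inferiority.

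Only if the claim of being no worse is to be kept, state before unblinding a margin for each named safety event (air leak, gastrointestinal perforation or bleeding, death), and require the upper 95% bound of the excess to lie below it. If the SAP already holds such a criterion, {20a} should refer to it.

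The rewording changes neither sample size nor conduct. Its cost is that the trial could make a weaker safety claim. Keeping the claim costs more: the margins need clinical justification, and at the present size some of them may not be attainable.

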### Strategies to improve adherence to interventions {11c}

Every effort will be made to allocate and initiate study treatment for enrolled (consented) and eligible infants as close to the time of extubation as possible, with no more than 2 h between extubation and initiation of allocated respiratory therapy. In the case of an unplanned extubation for an infant with informed consent, if the clinical team determines to provide a trial of non-invasive support, the infant will be allocated to study treatment as soon as possible, no later than 2 h after extubation.

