## Outcomes {12}

### Primary study endpoint

The primary study endpoint is extubation failure. Extubation failure is defined when an infant is on the allocated mode of respiratory support and meets any of the following four criteria: (1) rise in FiO_2_ at least 20% from pre-extubation value for > 2 h to maintain local SpO_2_ targets, (2) pH ≤ 7.20 or pCO_2_ ≥ 70 mmHg; (3) > 1 apneic event requiring positive pressure ventilation (PPV) within 6 h or ≥ 6 apneic events requiring stimulation within 6 h; (4) emergent intubation by the clinical team for cardiovascular instability or surgery; (5) any other intubation.

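### The primary model leaves out pre-extubation FiO2, a baseline value already needed to score failure criterion 1; adding it is an optional, low-cost gain

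*Protocol article*

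**What the plan says.** Under Statistical methods for primary and secondary outcomes {20a}, the protocol article specifies a GEE logistic regression clustered on the mother, and lists the adjustment terms: "The primary analysis will include clinical site, gestational age, biological sex, and days of invasive ventilation prior to extubation as fixed effects". The reason given there is residual confounding and site-level imbalance arising from the stratification factors. Sequence generation {16a} stratifies by site, gestational age group and time on ventilation. The model therefore covers every stratification factor and adds sex.

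The Primary study endpoint section makes the first failure criterion a "rise in FiO_2_ at least 20% from pre-extubation value for > 2 h to maintain local SpO_2_ targets". The section announces four criteria but numbers five. The other four (blood gas, apnea, emergent intubation, any other intubation) do not refer to baseline FiO2.

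Strategies to improve adherence {11c} also admits infants whose extubation was not planned. "In the case of an unplanned extubation for an infant with informed consent", allocation may follow up to 2 h after the event. Neither pre-extubation FiO2 nor extubation type is a stratification factor or a listed covariate. Table 5 collects ventilator settings at extubation but does not name planned versus unplanned status.

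The Sample size {14} section sizes the trial on "a two-sided proportions test", without covariates.

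**The concern.** In a logistic model, adjusting for a prognostic baseline variable raises the power of the treatment test and accounts for chance imbalance in that variable. Pre-extubation FiO2 is a natural candidate: criterion 1 cannot be scored without it, so it must be available for every infant, and it sets that infant's threshold on that criterion.

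Extubation type is a second candidate. The two routes into the trial may carry different risk, and they differ in one respect that the plan itself creates. Only infants randomised before extubation can be removed under the modified intention-to-treat rule for infants who are then not extubated.

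At stake is a modest amount of power, and protection against imbalance in an unblinded trial with two interim looks. The validity of the analysis is not at stake.

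**Working it through.** **Inputs from Sample size {14}.** "Sample size estimates were based on having 90% power to detect a 15% absolute risk reduction in extubation failure"; "assuming a two-sided test, family-wise error rate of 0.05 and a group sequential design with 2 interim analyses"; "we conservatively anticipate a 5-day extubation failure rate of 35% in the NS-NIPPV group", hence 20% under NIV-NAVA. Looks are at 50% and 75% with O'Brien-Fleming-type spending. The design effect is 1.15 and drop-out 2%.

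**Step 1: reproduce the plan's figures.**
- Fixed design, pooled variance: n per arm = [1.960·√(2·0.275·0.725) + 1.282·√(0.35·0.65 + 0.20·0.80)]² / 0.15² = 184.1, so 185 per arm, 370 in total.
- Continuity correction: (184.1/4)·[1 + √(1 + 4/(184.1·0.15))]² = 197.2, so 198 per arm, 396 in total.
- Simulated Lan-DeMets bounds are 2.96, 2.36 and 2.01. The drift needed for 90% power is 3.269, so inflation is (3.269/3.242)² = 1.017.
- 396 × 1.017 ≈ 403. The plan says "To detect a 15% absolute reduction in the rate of extubation failure rate in the NIV-NAVA group would require 406 infants", which is within 1%. Without the continuity correction the result is 370 × 1.017 ≈ 376, so 406 carries some margin.
- 203 per arm × 1.15 / 0.98 = 238.2, so 239 per arm and 478 in total, exactly as stated.

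**Step 2: effect of the added covariates.** The setup was as follows.
- 406 effectively independent infants (478 × 0.98 / 1.15 ≈ 407).
- Marginal failure rates of 35% and 20%.
- Wald test at the final-look critical value of 2.013.
- 12,000 simulated trials per row.

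Assumptions not in the document: 10% unplanned extubations, and one covariate already in the model with log odds ratio 0.5 per SD, standing in for the listed covariates.

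| Assumed OR per SD of FiO2 | Assumed OR, unplanned | Power without | Power with both terms | Gain (points) |
|---|---|---|---|---|
| 1.0 | 1.0 | 92.8% | 92.9% | 0.1 |
| 1.22 | 1.5 | 93.0% | 93.2% | 0.2 |
| 1.5 | 2 | 93.0% | 93.8% | 0.8 |
| 2 | 2 | 93.0% | 95.1% | 2.1 |
| 2.7 | 3 | 92.43% | 95.98% | 3.55 |

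With no association, nothing measurable is lost.

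**Step 3: shape of the FiO2 effect.** If the 20% rise is relative, a low baseline makes criterion 1 easier to meet, while sicker infants on high FiO2 may fail on other criteria. The net effect could be U-shaped. Fitting a linear term to such an effect (FiO2 only, 6,000 trials) gave 92.6% without and 92.5% with the term, so no gain.

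**Step 4: a second simulation.** It used 380 independent infants, gestational age and ventilation days already in the model, one added covariate, and 6,000 trials per setting at two-sided 0.05. For log odds ratios of 0.3, 0.5, 0.7 and 0.9 per SD, power rose from 91.6 to 92.0%, 92.5 to 93.2%, 92.2 to 93.8% and 91.6 to 94.7%. The gains of 0.4 to 3.1 points agree with Step 2.

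**Step 5: chance imbalance.** With N infants split 1:1, a standardised baseline difference has SD 2/√N. At the first look N ≈ 478/2 = 239, giving 2/√239 = 0.13. A gap above 0.25 SD is then 0.25/0.13 ≈ 1.9 SDs out, which happens in about 5% of trials.

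**Limits.** The simulations cover a single final test, omit site effects, and handle multiples only through the effective sample size.

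**The case against.** The case for leaving the model alone is strong. It adjusts for every stratification factor plus sex, for a stated purpose, and almost any trial could name one more plausible covariate. The trial was sized without covariates, reaches its target without these terms, and 478 would not change. The document gives no association of either variable with failure and no share of unplanned extubations, so the benefit is assumed. Enrolment has run since August 2022, so a new form item cannot cover infants already randomised. Supplementary adjusted models may also be in a statistical analysis plan that is not shown.

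Most of this stands, and it limits the point to a suggestion. It does not remove it. The covariate list for the primary analysis is written into the protocol, and FiO2 differs from an arbitrary extra covariate because scoring the endpoint already requires it.

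A reader might infer three stronger things that the document does not support:
- **That FiO2 determines the outcome by construction.** It is the reference for one criterion of five, and its net direction is unknown.
- **That the gain in power is certain or free.** It can be zero, and a linear term can miss it.
- **That the last FiO2 before randomisation is the right covariate for everyone.** After an unplanned extubation that reading may already be post-extubation. Before a planned one, the endpoint's reference value may be charted after randomisation.

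**Conclusion.** The point holds as an optional efficiency improvement. The stated model omits a baseline value that the trial must already hold. Including it, with extubation type where derivable, would be expected to add about 0 to 3.5 points of power, and under 1 point unless FiO2 is stronger than about OR 1.5 per SD. It would also account for chance imbalance.

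The range rests on assumed prognostic strengths, an assumed 10% of unplanned extubations, and an FiO2 term whose form fits the true shape. It would be wrong to conclude that the primary analysis is invalid or the trial underpowered: the design figures reproduce, and power without the added terms is about 92 to 93%.

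**What to change.** Before any unblinded look:

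1. Keep the four stated covariates and add the last FiO2 recorded before extubation or randomisation, whichever came first. This rule keeps post-extubation readings out for unplanned extubations and post-randomisation readings out for planned ones.
2. Prespecify a flexible form, such as a quadratic or a spline, rather than a single linear term.
3. Add planned versus unplanned extubation only if it can be derived for all infants from recorded extubation and randomisation times. Otherwise place it in a prespecified sensitivity analysis.

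No further infants and no change of endpoint are needed. The costs are one or two extra model terms and an odds ratio conditional on a slightly different covariate set, so it will differ a little from that of the stated model. Some chart retrieval may also be needed where the FiO2 held for criterion 1 was charted after randomisation. The document does not say whether the first interim look has taken place. If it has, the adjusted model is better kept as a sensitivity analysis.
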